### Randomisation method

The randomisation sequence will be generated using an independently verified S-PLUS program (Robertson Centre for Biostatistics, University of Glasgow, UK). This program uses a stratified permuted block randomisation procedure, with stratification based on the severity of walking impairment. This stratification will ensure that intervention groups are balanced, since severity of impairment influences the potential for recovery. Severity of walking impairments will be classified using the FAC. Stratification will consist of two groups: FAC 1 to 3, and FAC 4 to 5. The researcher will access intervention allocations through the study web portal, designed and maintained by The Robertson Centre for Biostatistics at the University of Glasgow. The randomisation sequence will be concealed until the participant’s details are logged on the system.

### Statistical analysis

Data will be analysed on an intention to treat basis. Data will be held independently on a database at the Glasgow Clinical Trials Unit at the University of Glasgow. Datasets for each randomisation allocation will be compared by independent blinded assessors.

Descriptive statistics will be calculated and the characteristics of the population will be described. Two mixed-design analysis of variance models will be used to test for mean differences between the three arms of the RCT, while subjecting participants to repeated measures. The repeated measures will be examined for differences over time and between groups. If appropriate, factors that may affect the outcome of the trial – such as differences in time since onset of stroke, age, severity of stroke or memory and attention levels – will be investigated using demographic and stroke-related information collected at baseline.

Data collected from pre-trial and post-trial interviews by the study researcher and in-depth semi-structured interviews by an independent researcher will be suitably coded such that qualitative responses can be categorised and explored.

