The primary outcome measure for this trial is walking speed, which will be measured using the 5-metre walk test [10]. Secondary outcome measures include the Functional Ambulation Category (FAC) [11], Timed Up and Go [12], Rivermead Visual Gait Assessment [13], spatial symmetry (ratio of step lengths) and temporal symmetry (ratio of step times), and the Stroke Impact Scale-16 [14]. Outcome assessments will be conducted at baseline, 6-week outcome and 6-month follow-up. The study physiotherapist will be present to assist participants during functional assessments only. The study researcher will be present to take measures and for technical support. To minimise patient burden during outcome assessments, participants will be instructed to do the 5-metre walk test four times and the Timed Up and Go test three times, if capable, while walking over a gridded mat and being video-recorded. From these recordings, an assessor blinded to treatment allocation will be able to assess all functional outcomes *post hoc*. The study researcher will help the participant complete the Stroke Impact Scale-16 questionnaire if required. Participants will be asked to complete a pre-trial questionnaire to determine what rehabilitation goals they may have and to obtain self-reported motivation and confidence levels. An additional questionnaire will be conducted by the study researcher at the 6-week outcome session. This will be used to gain further understanding of the impact and patient acceptance of the visualisation package. The questionnaire will explore whether the participant’s pre-trial goals have been achieved and the effects of the use of augmented visual feedback on patient motivation, confidence and understanding of their rehabilitation. The qualitative aspect of this research will be in the form of semi-structured interviews to gain further understanding of the impact of augmented visual feedback. These interviews will be carried out after participants have completed their 6-week outcome assessments. To reduce bias, an independent researcher, who has not been involved in the RCT, will be responsible for designing and conducting interviews with participants.

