### Sample size

A GPower *a priori* analysis for a mixed (2 × 3) analysis of variance was carried out. Setting α at 0.05 and 1β at 0.8, with an effect size of 0.2, this predicted a total sample size of 42. On this basis, and accounting for roughly a 10% drop out, we estimated that 45 participants (15 per group) would be sufficient to minimise the risk of type 1 or type 2 errors. We anticipate that results from this pilot study will yield data for a sample size estimation for a future definitive RCT.

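### Mixed-design ANOVA, unless paired with imputation, leaves out participants with a missing visit and so would not deliver the stated intention-to-treat analysis

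*Protocol article*

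**What the plan says.** The Statistical analysis section of the protocol article makes two commitments for the same data. The principle is: "Data will be analysed on an intention to treat basis". The method is: "Two mixed-design analysis of variance models will be used to test for mean differences between the three arms of the RCT". It adds: "The repeated measures will be examined for differences over time and between groups". It does not say which visits enter each of the two models.

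The Design section gives three time points: "Outcome assessments will be conducted at baseline, 6-week outcome and 6-month follow-up". It names walking speed as the primary outcome.

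The Sample size section expects losses. Having arrived at 42, it continues: "accounting for roughly a 10% drop out, we estimated that 45 participants (15 per group) would be sufficient". The Design section also lists the withdrawal or dropout rate as an adherence outcome.

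The article does not mention imputation, a likelihood-based model or the exclusion of incomplete participants.

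**The concern.** Intention to treat is usually taken to mean two things: participants are analysed in the arm to which they were allocated, and all randomised participants are included. Mixed-design ANOVA meets the first. It meets the second only if no visit in the model is missing or if missing values are filled in beforehand. The method works on a complete set of repeated measures per participant, and its default response to a gap is to remove the whole participant, including the values that were observed.

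Two things are at stake.

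- **Precision.** With 15 per arm, each participant removed costs information, and the trial is meant to inform the size of a definitive study.
- **Bias.** Contact differs by arm. Usual care may amount to no continuing therapy, while the placebo and intervention arms attend twice weekly for 6 weeks. Loss could therefore differ between arms in both amount and kind. If it is related to how much walking speed changes, a comparison restricted to complete cases can be biased.

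**Working it through.** **Inputs from the protocol article.** Three arms; visits at baseline, 6 weeks and 6 months; 45 randomised (15 per arm); dropout about 10%; alpha 0.05; power 0.80; effect size 0.2; calculated total 42.

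**Assumptions.** The effect size is Cohen's f, sphericity holds, and the correlation between visits is rho = 0.5. The article does not state rho, so a range of 0.3 to 0.8 is shown below.

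**Formula.** For the group-by-time interaction with g groups, m measurements and N participants:
- noncentrality = f² × N × m / (1 − rho)
- df1 = (g − 1)(m − 1)
- df2 = (N − g)(m − 1)

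**Step 1: reproduce the plan's figure.** The plan says "with an effect size of 0.2, this predicted a total sample size of 42". With g = 2, m = 3 and rho = 0.5, the noncentrality at N = 42 is 0.04 × 42 × 3 / 0.5 = 10.08, with df 2 and 80. Power is 0.803, so 42 is reproduced. With three groups at the same rho, the interaction needs 66 (two visits) or 54 (three visits). That mismatch, and whether 45 covers 10% dropout, are separate matters and do not decide this point. All three layouts are carried forward because the article does not settle which one applies.

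**Step 2: how many could be left out.** 45 × 0.10 = 4.5, so about 4 to 5 participants. 45 × 0.90 = 40.5 remain, taken as 40. At 20% loss, 45 × 0.80 = 36 remain.

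**Step 3: power with all 45 against complete cases only (f = 0.2, rho = 0.5).**

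| Layout | 45 | 40 | Fall | 36 |
|---|---|---|---|---|
| 2 groups × 3 visits | 0.832 | 0.782 | 0.05 | 0.733 |
| 3 groups × 2 visits | 0.635 | 0.576 | 0.06 | 0.525 |
| 3 groups × 3 visits | 0.726 | 0.664 | 0.06 | 0.608 |

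The column for 45 treats every participant as complete. Neither a mixed model nor imputation recovers all the lost information, so the fall is an upper bound on the gain.

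**Step 4: sensitivity to rho.** The same formula gives these falls from 45 to 40, for 2 × 3, 3 × 2 and 3 × 3 in turn:
- rho = 0.3: 0.057, 0.051, 0.059
- rho = 0.7: 0.021, 0.050, 0.038
- rho = 0.8: 0.004, 0.024, 0.010

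The loss never exceeds about 0.06, and it is small where power is already high.

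**Step 5: what each method does with gaps.** In one simulated data set (45 participants, three visits, about 5% loss before each follow-up visit), 38 participants were complete. A likelihood-based mixed model used all 45. A repeated-measures ANOVA routine rejected the incomplete data as unbalanced. This is a single draw and shows the mechanism, not an expected count.

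**Step 6: when the comparison is biased.** In one arm, let p be the fraction lost and d the mean change of those retained minus the mean change of those lost. The completers' mean change exceeds that of all randomised by p × d. The bias in the difference between arms 1 and 2 is p1 × d1 − p2 × d2. If those lost walk slower by the same amount at every visit, d = 0 and the group-by-time contrast is not biased. Bias needs loss that is related to change, and differently by arm. The article gives neither p by arm nor d, so no figure is put on it.

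**The case against.** A reader might infer that the two commitments in the Statistical analysis section cannot both be kept, and that the trial has in effect planned a completers analysis. The document does not support that. It nowhere says that incomplete participants are excluded. Deletion is the default of the named method, not a stated rule, and imputation before the ANOVA would reconcile the two sentences. Analysis by allocated arm, the other half of intention to treat, is not breached. A missing-data rule may also sit in an analysis plan that is not shown, so its absence from the article is not held against it here.

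Nor does the allowance in the Sample size section ("accounting for roughly a 10% drop out") prove a completers analysis. Trials are enlarged for dropout whatever the analysis set, because missing outcomes cost information in any analysis. In any case 45 less 10% is 40.5, not 42.

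It would also be too broad to say that anyone with any missing visit is lost altogether. There are two models with unnamed visits. If one covers baseline to 6 weeks, a participant missing only at 6 months stays in it.

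Finally, the trial is exploratory and the loss of power at the expected dropout is modest.

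All of this limits the point without removing it. The article commits to a specific method that, used as named, does not keep all randomised participants once visits are missing, and it expects participants to drop out. Even a baseline-to-6-week model removes someone without a 6-week value. A method that keeps them is readily available.

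**Conclusion.** The point stands in conditional form: without imputation, each mixed-design ANOVA excludes participants missing a visit that it uses, which falls short of analysing all randomised participants. At the protocol's own dropout this could affect about 4 to 5 of 45. The cost in power is at most about 0.05 to 0.06 at f = 0.2 and rho = 0.5, and between 0.004 and 0.06 over rho from 0.3 to 0.8.

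These figures assume that f is Cohen's f, that sphericity holds, and that every dropout lacks a visit used in the model concerned. Bias is a risk, not a demonstrated result: it arises if loss is related to change in walking speed differently by arm. The change is worth making before analysis, but the problem does not undermine the trial.

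**What to change.** In the Statistical analysis section, replace the mixed-design ANOVA as the main analysis with a likelihood-based linear mixed model that:

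- includes all randomised participants in their allocated arm;
- uses every available baseline, 6-week and 6-month value;
- contains arm-by-visit effects and the Functional Ambulation Category stratum used in randomisation (1 to 3, 4 to 5);
- applies a small-sample degrees-of-freedom correction.

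Estimate the between-arm differences from this model. Keep the complete-case mixed-design ANOVA as a sensitivity analysis and name the visits in each of its models.

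The cost is a change of wording and a little more analysis work in standard software; no extra data are needed. The model relies on data being missing at random given the observed values, which cannot be verified from the data. A participant with only a baseline value stays in the analysis but adds little information about the follow-up differences.

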**Methods:**

The hypothesis will be assessed using an exploratory (phase II) randomised controlled trial. Stroke survivors eligible for this trial will be in the subacute stage of stroke and have impaired walking ability (Functional Ambulation Classification of 1 or more). Participants (*n* = 45) will be randomised into three groups to compare the use of the visualisation software during overground physical therapy gait training against an intensity-matched and attention-matched placebo group and a usual care control group. The primary outcome measure will be walking speed. Secondary measures will be Functional Ambulation Category, Timed Up and Go, Rivermead Visual Gait Assessment, Stroke Impact Scale-16 and spatiotemporal parameters associated with walking. Additional qualitative measures will be used to assess the participant’s experience of the visual feedback provided in the study.

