### Primary research question

Will the early provision of augmented visual feedback of biomechanical movement performance in gait rehabilitation improve mobility outcomes after stroke?

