## Methods

### Design

The visualisation intervention will be tested in an exploratory (phase II) randomised controlled trial (RCT) [9]. See Figure3 for a flowchart of patient pathways. Participants will be randomised into three groups: a control group, a placebo group, and an intervention group that receives augmented visual feedback. 

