**Figure 3 F3:**
[figure not shown]
Outline of patient pathway in the randomised controlled trial.

Participants in the control group will continue with their usual care only. The term usual care refers to therapy provided by National Health Service (NHS) Lanarkshire, UK. This could be community care, day hospital care or no continued care, dependent on assessment of the patient’s ability by their clinical team.

In addition to usual care, participants in the placebo group will receive overground physical therapy gait training. Gait training will be provided as 1-hour sessions, twice weekly for 6 weeks. This training will consist of walking practice and a predetermined pool of walking-related exercises that study physiotherapists can choose from. The exercises are based on hip, knee and ankle range of motion in sitting and standing. Participants in this group will not receive any augmented visual feedback of their movement. The study physiotherapist will provide participants with feedback by demonstration and verbal feedback only, as per conventional gait training. During gait training, participants’ movements will be recorded using 3D optical motion capture. This will involve placing small reflective markers on the pelvis and lower limb segments.

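### The primary question is about visual feedback, but the stated test compares all three arms at once and cannot separate feedback from extra therapy

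*Protocol article*

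**What the plan says.** All references are to the protocol article.

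- **Primary research question:** "Will the early provision of augmented visual feedback of biomechanical movement performance in gait rehabilitation improve mobility outcomes after stroke".
- **Design, arms:** "Participants will be randomised into three groups: a control group, a placebo group, and an intervention group that receives augmented visual feedback".
- **Design, control arm:** "Participants in the control group will continue with their usual care only".
- **Design, placebo arm:** "In addition to usual care, participants in the placebo group will receive overground physical therapy gait training". The dose is fixed: "Gait training will be provided as 1-hour sessions, twice weekly for 6 weeks". The intervention arm has the same session length, frequency, duration and pool of exercises. It also has the stick-figure display and virtual targets.
- **Abstract, Methods:** the software is to be compared "against an intensity-matched and attention-matched placebo group and a usual care control group".
- **Design, outcomes:** walking speed is primary. "Outcome assessments will be conducted at baseline, 6-week outcome and 6-month follow-up". Neither follow-up is ranked above the other.
- **Statistical analysis:** "Two mixed-design analysis of variance models will be used to test for mean differences between the three arms of the RCT". The repeated measures are then to be examined for time differences and group differences. The section does not say what the two models are, which effect decides, or which pair of arms matters most.
- **Sample size:** a total of 42 from a mixed 2 × 3 ANOVA (alpha 0.05, power 0.8, effect size 0.2), raised to 45, or 15 per group.

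**The concern.** The design can answer the primary question, because placebo and intervention receive the same extra physiotherapy (2 sessions × 6 weeks = 12 sessions of one hour) and differ by the feedback package. Usual care differs from both in the amount of therapy. The stated analysis does not use this structure. A test of any difference among three arms responds equally to feedback helping and to extra physiotherapy helping.

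The other effects an ANOVA produces do not fill the gap. The time effect pools the arms, and so mixes recovery within three months of stroke with training given to two of the three arms. The group main effect averages the pre-treatment baseline into each arm's mean, which dilutes any benefit.

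At stake is how a positive result is read. The Discussion expects the results to confirm benefits of visualisation and to power a larger trial. If the difference seen comes from added therapy hours, that reading would be wrong and the next trial could be mis-sized.

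**Working it through.** **Inputs.** From the documents: three arms; 42 participants before dropout, so 42/3 = 14 per arm; 15 per arm enrolled; two-sided alpha 0.05; effect size 0.2, taken as Cohen's f. Not in the documents, so assumed: a between-person SD of walking speed set to 1; a correlation ρ of 0.5 to 0.7 between assessments; effects of 0.3, 0.5 and 0.8 SD.

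**1. The plan's own figure.** For an interaction with m time points, λ = f²·N·m/(1−ρ).
- Two groups at three times, ρ = 0.5: λ = 0.04 × 42 × 3/0.5 = 10.08, power 0.803. This reproduces 42.
- Three groups at two times, ρ = 0.5: λ = 0.04 × 42 × 2/0.5 = 6.72, power 0.60. This reading needs 66 participants, and comes down to about 42 only at ρ of about 0.7.

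The article does not say which factor has two levels. Neither reading describes intervention versus placebo at one time point: those two arms hold 28 to 30 people, not 42.

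**2. The interaction when training works and feedback does not.** With baseline and one follow-up, the group-by-time interaction is the one-way F test on change scores, whose variance is 2(1−ρ). The mean gains are (0, d, d) for usual care, placebo and intervention. Their squared deviations sum to (4/9 + 1/9 + 1/9)d² = (2/3)d². Hence λ = n(2/3)d²/[2(1−ρ)] on 2 and 39 df.

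| d (SD) | λ, ρ = 0.5 | Significant | λ, ρ = 0.7 | Significant |
|---|---|---|---|---|
| 0.3 | 0.84 | 11% | 1.40 | 16% |
| 0.5 | 2.33 | 24% | 3.89 | 38% |
| 0.8 | 5.97 | 55% | 9.96 | 78% |

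Intervention and placebo have equal means here, so their contrast rejects at its nominal rate, about 5%.

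**3. The interaction when only feedback works.** The gains are (0, 0, d). The squared deviations again sum to (2/3)d², so λ and every percentage in the table are unchanged. The omnibus p-value cannot tell the two situations apart. In this second situation, at 0.8 SD, intervention versus placebo on change scores has power 0.53 (ρ = 0.5) to 0.75 (ρ = 0.7), against 0.55 to 0.78 for the interaction. Naming the contrast costs almost no power.

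**4. The group main effect.** Averaging baseline and follow-up halves the shift to d/2 and gives variance (1+ρ)/2, so λ = n·d²/[3(1+ρ)]. At d = 0.8 and ρ = 0.5, λ = 14 × 0.64/4.5 = 1.99 and power is 0.21; at ρ = 0.7 it is 0.19. Adding a second follow-up at which the effect persists (15 per arm, ρ = 0.5, simulated) raises it to 0.42. That is still below the interaction's 0.61 in the same model.

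**5. The two models.** If they are baseline to 6 weeks and baseline to 6 months on walking speed, each tested at 0.05, simulation gives a familywise error of about 8-9%. With independent tests it would be 1 − 0.95² = 9.75%.

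**6. Power of the named contrast.** For an unadjusted t test at one time point, 80% power needs a difference of 1.10 SD at 14 per arm or 1.06 SD at 15 per arm. At 15 per arm, power is 0.26 for 0.5 SD and 0.56 for 0.8 SD.

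**The case against.** The strongest reply is that this is a condensed article of an exploratory trial. Follow-up contrasts after an ANOVA are commonly left to the analysis plan, and the Abstract does name both comparators. Nothing says that a significant omnibus test alone will be read as a feedback effect, and an ordinary intervention-versus-placebo follow-up would reject in only about 5% of trials if feedback did nothing.

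Much of this stands. A reader might infer that the trial will claim a feedback effect from the omnibus result; the documents do not say so, and the harm arises only if the pairwise step is skipped or its choice is left until after the data are seen. What remains is that the article does state a test, and that test does not match its stated question. Naming two comparators in the Abstract does not say which one decides.

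Three stronger readings are tempting and unsupported:

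- *Alpha is inflated because there are two models.* The article does not define them or tie both to walking speed. They may be one per follow-up, one per outcome, or something else. The 8-9% belongs to the first reading only.
- *A significant group effect is likely even if feedback does nothing.* With two time points the group main effect rejects only about 20% of the time at 0.8 SD. The interaction passes one half only for training effects near 0.8 SD, a size the documents do not give.
- *The time effect is simply natural recovery.* It also contains training in two arms.

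**Conclusion.** The concern holds in a limited form. The primary question needs intervention versus placebo; the stated analysis tests differences among three arms and ranks no contrast, effect or time point. With 14 per arm and two time points, the interaction is significant in about 11-16%, 24-38% and 55-78% of trials for effects of 0.3, 0.5 and 0.8 SD, whether those effects come from training alone or from feedback alone. Neither the group main effect nor the time effect is evidence of a feedback benefit.

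That the omnibus test cannot separate the two explanations follows from the design and needs no assumed effect size. The percentages rest on the assumed effects, correlations of 0.5-0.7, normality and complete data.

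A reader might take this as a flaw that invalidates the trial. The documents do not support that: the trial is described as phase II and as a pilot, the randomised comparison needed is present, and the remedy is wording. It should be fixed because it is cheap.

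**What to change.** In Statistical analysis:

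- Name intervention minus placebo in walking speed at one prespecified time point as the primary comparison, reported as an estimate with a 95% CI. The 6-week end-of-training assessment is one candidate. The article does not rank the two follow-ups, so the sponsor must confirm the choice.
- Make intervention versus usual care, placebo versus usual care and the other time point secondary.
- State that the time effect, the group main effect and the omnibus interaction will not by themselves be taken as evidence for feedback.
- Say what the two models are. If both test walking speed, say which one is primary.

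In Sample size, restate the power. The present statement does not apply to this contrast, which has 80% power only for about 1.06-1.10 SD unadjusted. Adjusting for baseline multiplies that by about √(1−ρ²): 0.87 at ρ = 0.5 and 0.71 at ρ = 0.7, giving roughly 0.92-0.95 and 0.76-0.79 SD.

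The cost is a wording change with no new data or visits. The drawbacks are that the usual-care contrasts and one follow-up lose primary standing, and that the article must admit limited power for its main question. That is a reason to lead with the interval rather than the p-value.

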### Identification of eligible patients

Participants will be recruited from acute sites and community rehabilitation teams in NHS Lanarkshire, UK. For full inclusion/exclusion criteria refer to Table 1. Potential participants will be identified by their NHS direct care team and/or stroke research nurses, who will ensure that the patient is able to give informed consent with suitable communication support if required. Written informed consent will be obtained from all participants prior to participation in the study.

**Table 1 T1:** Inclusion and exclusion criteria

**Inclusion criteria**	**Exclusion criteria**
· Clinical diagnosis of stroke	· Severe visual or cognitive problems precluding participation in the study
· In the subacute stage of stroke (≤3 months since stroke onset)	· Involved in another physical rehabilitation research trial
· Of either gender	· Pre-existing lower limb deficits or any other medical comorbidities that interfere significantly with gait.
· Age ≥18 years	
· Exhibit an abnormal gait pattern Functional Ambulation Category of 1 or more	
· Medically stable and hence suitable for physical rehabilitation	
· Able to understand and follow simple instructions	
· Able to give informed consent when assisted to do so with suitable communication aids if required	

The research nurse or researcher will go over the study’s participant information sheet with the patient. Patients will have the opportunity to ask any questions and will be given a minimum of 24 hours to review the information sheet and consider their participation in the trial. During this time they will be able to ask any further questions and talk to other people about the study. The research nurse or researcher will then approach the patient again, answer any further questions and, if appropriate, gain consent from the patient who is to sign a consent form. This study complies with data-protection legislation. Upon enrolment in the study, patients will be allocated a unique trial number that will be used in all case-report file documents. Patient names will be used to arrange appointments only and will not be used for data-collection purposes. Where a patient is deemed eligible and provides informed consent, the following demographic and stroke information will be collected: age, sex, postcode, date of stroke, side affected, dominant side, pre-stroke function (FAC score) and type of stroke (Oxford Stroke Classification) [18].

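### Pre-specifying baseline walking speed and the FAC randomisation stratum as covariates would be more precise than the planned mixed-design ANOVA, at almost no cost

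*Protocol article*

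**What the plan says.** All references are to the protocol article; no separate analysis plan is at hand.

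- **Outcome (Methods, Design).** "The primary outcome measure for this trial is walking speed, which will be measured using the 5-metre walk test". Assessments are at baseline, 6 weeks and 6 months.
- **Model (Statistical analysis).** Two mixed-design ANOVA models compare the three arms, and "The repeated measures will be examined for differences over time and between groups". No sentence names baseline walking speed as a covariate.
- **Stratification (Randomisation method).** Allocation is stratified by FAC 1 to 3 against FAC 4 to 5. The reason given is "This stratification will ensure that intervention groups are balanced, since severity of impairment influences the potential for recovery". The analysis section names no stratum term.
- **Other covariates (Statistical analysis).** Time since stroke, age, stroke severity, memory and attention are offered as examples of factors that, conditionally, "will be investigated using demographic and stroke-related information collected at baseline". The list of demographic and stroke items gives age, sex and postcode, then "date of stroke, side affected, dominant side, pre-stroke function (FAC score) and type of stroke (Oxford Stroke Classification".
- **Sample size.** The calculation was done in GPower for a mixed ANOVA described as 2 by 3. Its inputs and result read: "Setting α at 0.05 and 1β at 0.8, with an effect size of 0.2, this predicted a total sample size of 42". The allowance for attrition is put this way: "accounting for roughly a 10% drop out, we estimated that 45 participants (15 per group) would be sufficient".

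**The concern.** When baseline is one level of time, the arm-by-time test for baseline against a follow-up visit compares changes from baseline. A change score subtracts the whole of the baseline value, whereas a regression on baseline subtracts only the part that predicts follow-up. The excess subtraction carries chance baseline imbalance into the estimate. With 15 per arm such imbalance can be sizeable and precision is scarce.

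The stratum raises a related point. The protocol itself regards walking severity as prognostic and builds it into the randomisation, but does not carry it into the stated model.

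What is at stake is the width of the confidence intervals and the power of the arm comparisons. It also touches the effect and variance estimates that the protocol intends to use to size a definitive trial.

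**Working it through.** **1. The plan's own figure.** Inputs from Sample size: alpha 0.05, power 0.80, effect size 0.2 (read as Cohen's f; the index is not named), N = 42. For the interaction in a repeated-measures ANOVA with m measurements and correlation r, the noncentrality is λ = f²·N·m/(1−r).

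- Two groups by three measurements, r = 0.5: λ = 0.04 × 42 × 3/0.5 = 10.08, power 80.3%. This reproduces 42.
- Three arms by two times, r = 0.5: λ = 0.04 × 42 × 2/0.5 = 6.72, power 60.1%, and 66 participants are needed. This layout gives 42 only at r of about 0.7.

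The document states neither the correlation nor which factor has two levels, so r has to be varied.

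**2. Change against baseline adjustment.** Take one follow-up visit, equal SDs (set to 1) and correlation r. Both quantities below are proportional to the variance of an arm difference.

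- Change score: 2(1−r)
- Baseline-adjusted: 1−r²
- Ratio, adjusted to change: (1+r)/2

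The difference is 2(1−r) − (1−r²) = (1−r)², which is the contribution of chance baseline imbalance.

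Power below is for three arms by two times with f = 0.2 and N = 42. For the adjusted analysis, λ is multiplied by 2/(1+r) and one error degree of freedom is given up.

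| r (assumed) | Change | Adjusted | Saving | Power, change → adjusted | N for 80% |
|---|---|---|---|---|---|
| 0.5 | 1.00 | 0.75 | 25% | 60.1% → 73.3% | 66 → 51 |
| 0.6 | 0.80 | 0.64 | 20% | 70.4% → 80.3% | 54 → 42 |
| 0.7 | 0.60 | 0.51 | 15% | 83.0% → 88.8% | 42 → 36 |
| 0.8 | 0.40 | 0.36 | 10% | 95.1% → 96.9% | 30 → 27 |
| 0.9 | 0.20 | 0.19 | 5% | 99.9% → about 100% | 18 → 18 |

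**3. Unequal SDs.** If the follow-up SD is k times the baseline SD, the change variance is 1 + k² − 2rk and the adjusted variance is k²(1−r²). With k = 1.25 (an assumption):

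- r = 0.5: 1.3125 against 1.1719, saving 11%
- r = 0.7: 0.8125 against 0.7969, saving 2%
- r = 0.8: 0.5625 against 0.5625, no saving

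If the SD shrinks over follow-up, the saving is larger.

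**4. The FAC stratum.** This was simulated with 45 patients, strata split 8/7 in each arm, one arm shifted by 0.7 SD and 3,000 runs. The prognostic strength of the stratum was varied over five settings, all assumed.

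- Adding FAC to a change-score model lowered variance by 0–2%.
- Adding FAC to a model that already had baseline speed lowered it by a further 3–19%. An example is 0.1143 to 0.1022, which is 11%.
- Baseline speed and FAC together, against the change score, lowered it by about 13–25%. The extremes were 0.0802 to 0.0699 and 0.1361 to 0.1022.

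Baseline speed gave the larger part of the gain in four of the five settings. In the fifth, the less impaired or more impaired stratum was given extra recovery beyond what baseline speed predicts, and FAC gave the larger part.

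**The case against.** The strongest reply is that this is a condensed article. Exact model terms, including stratum adjustment, are commonly left to an analysis plan that is not shown, and the covariate list is open-ended and includes severity. That stands as far as it goes: a reader might infer that the stratum has been deliberately excluded, and silence does not show this. Baseline as a level of time is likewise inferred, from the three assessments and the stated interest in differences over time. But the article does fix the class of model. If time meant only the two follow-up visits, baseline speed would still not be a named covariate and the remedy would be the same.

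The size of the gain is also open to challenge, and fairly so. It depends on a correlation and an SD ratio that the document does not give. The formula describes baseline against one follow-up visit, while there are three assessments. At high correlation, or with an SD that grows over follow-up, little is saved. Stratifying by FAC already limits imbalance in walking severity, and the trial is exploratory.

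Three stronger readings are not supported:

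- **Covariates chosen after seeing results.** The text speaks of differences in patient characteristics, not in outcomes. The Design section names attention and memory in advance as possible covariates and measures them at baseline. The conditional wording is loose, but no more than that.
- **Stroke severity not collected.** The demographic list has no item labelled as severity. However, the baseline session includes FAC, Timed Up and Go, the Rivermead gait assessment and the Stroke Impact Scale-16, besides tests of memory and attention. The term is undefined; data are not shown to be missing.
- **An invalid or biased test.** Under randomisation the arm-by-time comparison is valid.

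**Conclusion.** The point holds as a loss of efficiency in the planned analysis. For a two-time contrast with equal SDs, baseline adjustment saves about 25% of the variance at r = 0.5, 15% at 0.7, 10% at 0.8 and 5% at 0.9. At r = 0.5 the saving is worth 1/0.75 = 1.33, or about a third more participants. The saving falls to between 0% and 11% over r = 0.5 to 0.8 if the follow-up SD is 1.25 times baseline. The power figures also assume that 0.2 is Cohen's f and that time has two levels, so they illustrate the gain and do not predict it.

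Most of the gain is likely to come from baseline speed. FAC usually adds a smaller amount, and including it makes the analysis match the randomisation. It would be wrong to say that omitting FAC alone makes the planned standard errors materially too wide, since it changed a change-score analysis by no more than 2% in simulation. This is a worthwhile improvement, not a flaw that undermines the trial.

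**What to change.** In Statistical analysis, replace the mixed-design ANOVA over all visits with a model of 6-week and 6-month walking speed by arm. This can be ANCOVA at each visit or a repeated-measures model of the two follow-up visits. Name baseline walking speed and the FAC randomisation stratum (1 to 3, 4 to 5) as pre-specified covariates. Use the same form, with the matching baseline value, for the continuous secondary outcomes.

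Label age, time since stroke, memory and attention as exploratory covariates. Define stroke severity by a measure already collected, or drop the term.

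The cost is small: no extra patients, visits or measurements. The Sample size paragraph rests on a mixed ANOVA and should be restated for the new model, giving the assumed correlation and the comparison it refers to.
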